## Introduction

Tuberculosis (TB) disease, which kills 1.5 million people annually, is driven by poverty
^1^. Having TB disease can also worsen impoverishment through loss of income and costs of accessing care
^2–
5^. Such costs can become “catastrophic”, leading patients to abandon treatment, develop drug-resistance, and die
^6^. WHO’s 2015 End TB Strategy advocates elimination of catastrophic costs and provision of socioeconomic support for TB-affected households
^5^. Nevertheless, there is minimal evidence concerning the ideal interventions to realise this policy change
^6–
10^. This research will generate preliminary evidence to fill this knowledge gap in a low-income country: Nepal. The findings will inform a randomised controlled trial of socioeconomic support for TB-affected households in Nepal.

Research from Peru has demonstrated that the severe socioeconomic impact of TB can lead to catastrophic costs (defined by WHO as >20% of a household’s annual income)
^6^. The same team also demonstrated that socioeconomic interventions for TB-affected households can mitigate catastrophic costs (
Figure 1a), improve TB preventive therapy uptake (
Figure 1b), and increase TB treatment success (
Figure 1c)
^11–
15^.

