**Figure 1. f1:**
[figure not shown]
**a**) Catastrophic costs incurred by intervention (n=135) and control (n=147) TB-affected households of Callao, Peru.
**b**) Preventive therapy initiation in household contacts of intervention (n=206) and control (n=204) TB-affected households of Callao, Peru.
**c**) TB treatment success in patients from intervention (n=135) and control (n=147) TB-affected households of Callao, Peru. Part
**a**) has been reproduced with permission from Wingfield
*et al.*
^13^ Parts
**b**) and
**c**) have been reproduced with permission from Wingfield
*et al.*
^15^.

However, despite these encouraging findings, Peru is a middle-income country with a strong TB program and existing national cash-transfer schemes. To make this research replicable and applicable in diverse settings, interventions similar to those in Peru need to be adapted to other country contexts, especially low-income countries (LICs) with less developed social protection schemes and high TB burden. One such country is Nepal.

The estimated incidence of TB in Nepal is 154/100,000 people with 45,000 cases of TB being notified. Amongst these cases, there were 6,800 TB-related deaths. Multi-drug resistance (MDR) rates were 2.2% in new cases and 15% among retreatment cases. Importantly, despite good treatment success rates overall of more than 90% reported in Nepal, there remain shortcomings in TB care: treatment success rates were 70% for patients with MDR-TB and only 9% for those with HIV-TB co-infection; and accessibility of TB care remains low with treatment coverage of 70%
^16^.

The poor treatment coverage in Nepal may, in part, be due to the financial impact on TB-affected households, which is estimated to be high
^17^. Responding to this estimated burden, the Nepal National TB Programme (NTP) national strategic plan for 2016–2021 identifies provision of a support package to TB-affected households (specifically targeting MDR-TB-affected households) as a priority aim for the country with the goal of reducing catastrophic costs. There is currently limited evidence concerning the potential acceptability, impact, or cost-effectiveness of such a package, with which to inform and guide this policy decision. A cohort study has suggested that, during their illness, TB patients in Nepal experience decreased income and the total costs of accessing free TB treatment equate to nearly one quarter of annual household income

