### Study population

***Participant identification, recruitment and follow-up***. During Project 1, approximately 200 people with TB (cases) consecutively recruited to Work Package 3 (WP3) of IMPACT-TB (Health Economic Analysis) in the four study sites will be further recruited to this study. 100 of these cases will have been diagnosed through ACF and 100 diagnosed through PCF. Whilst attending the NTP TB clinic, these people with TB will be invited to participate in this mixed-methods research with a separate written, informed consent (see Project 1 Interview Patient Consent Form,
*Extended data*)
^29^. During months three and six of their TB treatment, household visits will be conducted by BNMT project staff including community mobilisers.

Concurrently, 100 people without TB from the study sites (controls) will be invited to participate with written, informed consent (see Project 1 Interview Healthy Control Consent Form,
*Extended data*)

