### Data analysis and statistical plan

The quantitative data collected during the household visits of Project 1 will be analysed using simple descriptive statistics. Continuous costs data will be summarised by their arithmetic means and their 95% confidence intervals whether the data is Gaussian or non-Gaussian, because this approach is considered to be robust for health economics data analysis
^6,
34–
36^. Furthermore, because of the skewed nature of some expenditure data, median values may be zero or close to zero limiting the descriptive usefulness of presenting median values. As described in the PI’s previous research
^6^, any direct expenses, lost income, or annual income recorded as “zero” or missing will be replaced with the mean cost of each costs category, i.e. mean direct costs or lost income. The local currency, Nepalese rupee, will be converted into United States Dollars (conversion rate and date estimated through
Oanda at time of data collection). Categorical data will be summarised as proportions with 95% confidence intervals.

With regards to analysis of household income and expenditure, the WHO TB Patients Costs Survey methods will be followed. In order to evaluate the optimal analytical strategy for costs data in Nepal, the analysis will compare and contrast the different approaches used in the WHO Survey to estimate household income (self-reported household consumption; self-reported household expenditure; self-reported household income; and estimated income based on household asset ownership and dwelling characteristics) and lost income (output approach of reported income pre- and during TB versus human capital approach of multiplying hours of work lost by hourly rate or daily in rate in cases of hospitalised patients).

Social determinants of TB including sociodemographic characteristics, socioeconomic position, stigma and social capital levels, and TB-related knowledge will be compared between ACF patients, PCF patients, and controls using Chi-squared test, Pearson’s test, one-way ANOVA, and multiple logistic regression models where appropriate. No comparison will be made between patients and controls concerning healthcare expenditure as this data was not collected from controls. Statistical analysis will be performed using the statistical software package STATA v13.1 (Statacorp, TX, USA).

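### Recorded zeros are treated as missing and filled with means: zero-income households get an average denominator, zero-cost households get an average cost, and the pattern of catastrophic costs by income is distorted

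*Protocol article*

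**What the plan says.** The section on data analysis and the statistical plan covers three variables in one rule. It applies to "any direct expenses, lost income, or annual income recorded as “zero” or missing"; for income it reads "annual income recorded as “zero” or missing will be replaced with the mean cost of each costs category", and the mean is spelled out as the "mean cost of each costs category, i.e. mean direct costs or lost income". Recorded zeros and missing values get the same treatment. The clause that explains which mean is used names direct costs and lost income, but nothing for annual income.

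The Introduction gives the WHO definition: "catastrophic costs (defined by WHO as >20% of a household’s annual income". Annual income is therefore the denominator of the cost burden, and the other two variables form the numerator.

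The same analysis section says that WHO survey methods will be followed. It plans to compare several ways of estimating household income, including "estimated income based on household asset ownership and dwelling characteristics". It neither exempts any of these from the replacement rule nor links them to it. It also accepts that zeros are common in expenditure data: "median values may be zero or close to zero limiting the descriptive usefulness of presenting median values".

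**The concern.** A zero is an observation. A household that reports no income and has any TB cost lies at the extreme of the burden measure. A household that paid nothing, or lost no income, lies at the other end on that component. Replacing both with means pulls them towards the middle from opposite directions.

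Project 1's primary aim is the socioeconomic impact on TB-affected households and its comparison by route of diagnosis: "100 of these cases will have been diagnosed through ACF and 100 diagnosed through PCF". The findings are to inform the protocol of a later trial of socioeconomic support. If the burden is moved from households without income to earning households, the evidence on whom to support is distorted, even if the overall proportion looks plausible. If zeros are more frequent in one diagnostic group than in the other, that comparison is affected too.

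**Working it through.** The protocol gives no zero shares, expected prevalence or power calculation, so there is no figure to reproduce.

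**1. Logic.** Let D be direct cost, L lost income and Y annual income. A household is catastrophic if (D + L) / Y > 0.20.

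- Y = 0 and D + L > 0: truly catastrophic. Under the rule it is flagged only if its filled cost exceeds 0.20 × mean income, so it can only lose the flag.
- Y = 0 and D + L = 0: no cost. Under the rule it receives both mean costs, so it can only gain the flag.
- Y > 0 with D = 0 or L = 0: the numerator rises, so it can only gain the flag.
- All three positive: unchanged.

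**2. Illustration.** Only the 20% threshold comes from the protocol. Assumed: positive incomes lognormal, median 1,200, log-SD 0.9; positive D and L each lognormal, median 90, log-SD 1.0; 10% zero incomes; 20% zero D; 40% zero L among earners; L = 0 in zero-income households; fill-in value = mean of the positive values.

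- Mean income = 1,200 × exp(0.81/2) = 1,799, so the filled threshold is 0.20 × 1,799 = 360.
- Mean positive D or L = 90 × exp(0.5) = 148.
- Zero income, D = 0 (20%): 148 + 148 = 297 (unrounded means), below 360, so never flagged.
- Zero income, D > 0 (80%): flagged if D > 360 − 148 = 211. The probability is 1 − Φ(ln(211.4/90)) = 1 − Φ(0.854) = 0.197.
- Zero-income households: true 0.80; reported 0.80 × 0.197 = 0.157.
- Earners, by simulation: true 0.329; reported 0.509.
- Overall: true 0.1 × 0.80 + 0.9 × 0.329 = 0.376; reported 0.1 × 0.157 + 0.9 × 0.509 = 0.474.

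In 200 cases, 20 would have zero income, with 16 truly catastrophic and about 3 reported. Of 180 earners, about 59 would be truly catastrophic and 92 reported.

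**3. Overall direction.** Same distributions, other zero shares, by simulation:

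| Zero Y / D / L | Overall, true → reported |
|---|---|
| 10% / 20% / 40% | 37.6% → 47.4% |
| 10% / 0% / 30% | about 46% → 46% |
| 20% / 10% / 30% | about 48% → 43% |

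In the second row nothing seems wrong overall, yet zero-income households fall from 100% to 20% and earners rise from 40% to 49%.

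**4. Sensitivity to cost level.** In step 2, mean cost over mean income is (0.8 + 0.9 × 0.6) × 148.4 / (0.9 × 1,799) = 199/1,619 = 12%. The Introduction (text after Figure 1) cites a cohort in which "the total costs of accessing free TB treatment equate to nearly one quarter of annual household income". Raising the cost median to 183 brings the ratio to 0.25, and the mean fill-in becomes 183.2 × exp(0.5) = 302.

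- Zero income, D = 0: 302 + 302 = 604, above 360, so all are flagged (20 points falsely gained).
- Zero income, D > 0: flagged if D > 58, probability Φ(1.155) = 0.876, which gives 0.80 × 0.876 = 0.70 (10 points lost).
- Reported 90% against 80% true, with 30% of these households misclassified. Earners go from 52% to 75% (simulation).

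A separate calculation at the one-quarter ratio assumed a positive direct cost in every zero-income household, lost income at 30% to 70% of cost, and cost CV 0.5 to 1.5. It found 2% to 59% of zero-income households hidden.

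**5. Mean costs.** If a fraction f of values are true zeros, filling with the non-zero mean overstates the mean by 1/(1 − f) − 1: 11%, 43% and 100% for f = 10%, 30% and 50%.

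**6. Repairing income alone.** With step 2's inputs, keeping zero income but still filling costs flags every zero-income household: 0.1 × 1.00 + 0.9 × 0.509 = 0.558, against 0.376 true.

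**The case against.** The strongest reply is that the rule works on numerator and denominator together, so a simple claim of understated prevalence fails. That stands. A reader might infer that the rule hides the catastrophic costs of the poorest and lowers the overall proportion. The protocol does not support this: step 3 shows the overall figure rising, unchanged or falling. Nor do missing incomes identify the poorest. That argument applies at most to recorded zeros, and even a self-reported zero need not mean poverty.

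Other points also carry weight. The study is exploratory, and its list of outcomes does not name catastrophic costs. They enter through the Introduction and the WHO survey methods. Socioeconomic position is measured by a separate poverty score, which the rule does not touch. The planned comparison of income estimates could expose the problem, because consumption- and asset-based denominators need not use self-reported income. However, it is not tied to the replacement rule and does nothing for zero costs. That the rule follows earlier research explains it but does not justify it.

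Read literally, the rule puts a cost in the place of an income. This is more likely loose drafting than intent, but the value to be used for income still has to be stated.

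**Conclusion.** The point holds in this form: the stated rule treats observed zeros as missing in all three variables. It misclassifies zero-income households and earners with zero costs, and it names no replacement value for income. The direction for each type of household follows from the definition alone. The sizes do not: they rest on assumed distributions and zero shares that the protocol does not give.

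At the lower cost level, most zero-income households are reclassified as not catastrophic (80% true, 16% reported) and the gradient by income reverses. At the one-quarter cost ratio the losses are smaller and false gains can outweigh them. The net change in overall prevalence is undetermined, so no single figure for its bias should be quoted.

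**What to change.** - Limit the replacement rule to values that are truly missing. Keep recorded zeros in direct expenses and lost income as zeros.
- Where annual income is zero or missing, use that household's own asset- and dwelling-based or consumption-based estimate, both already planned. Never use a sample mean or a cost.
- In the version based on self-reported income, keep a true zero and class the household as catastrophic only if its actual recorded TB cost is above zero.
- Make these changes together. Step 6 shows that correcting income alone would overstate prevalence further.
- Report the number of households affected for each variable, and show the mean-replacement rule as a sensitivity analysis only.

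The cost is revised wording and some extra analysis code. The protocol reports household-visit data collection as nearly complete and analysis as not yet begun, so no new data are needed, provided that the database holds zeros and blanks separately. The results will be less directly comparable with the earlier research that used the rule; the sensitivity analysis keeps that link.

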### Study design

This mixed-methods study was funded by a Wellcome Trust Seed Award in Science (awards provided to early-career researchers to develop a novel idea that will go on to form part of a larger grant application) and will be divided into two complementary projects. Project 1 consists of a cohort study characterising the socioeconomic impact of TB on TB-affected households and a nested case-control study examining the social determinants of TB. Project 2 consists of a mixed quantitative-qualitative cross-sectional study using surveys, FGDs and a workshop to identify the barriers and facilitators to accessing and engaging with TB diagnosis and care in Nepal and suggesting potential interventions to mitigate the socioeconomic impact and improve access and engagement. The study will take place within the infrastructure of the larger EU-Horizon 2020 funded “IMPACT-TB” project, which is a study evaluating proven TB active case-finding (ACF) interventions in Nepal and Vietnam (grant 733174,
http://www.impacttbproject.org/).

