### Secondary aims

The secondary aim of Project 1 is to compare the social determinants of TB (including socioeconomic position, housing situation, knowledge about TB, comorbidities, quality of life, food security, and social capital) in people with TB versus people without TB from the same districts. The secondary aim of Project 2 is to collate the opinions of key stakeholders from diverse sectors about barriers and facilitators to accessing and engaging with TB care in Nepal.

An additional aim across the study is to generate a policy dialogue and form a collaborative research network to support development and implementation of a future randomised control trial of socioeconomic support for TB-affected households in Nepal.

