### Study activities

Broadly, the activities involved in the research will include interviews with Cases and Controls during household visits, and a pre-FGD survey, FGD, and workshop with key stakeholders.

During Project 1, the project team will support BNMT district coordinators, community mobilisers, and community volunteers to do household visits to approximately 200 Cases with TB (100 diagnosed through ACF and 100 through PCF) recruited to WP3 of the IMPACT-TB project. People with TB will receive two household visits, the first during month three of TB treatment and the second visit during month six of TB treatment (to correspond with treatment completion). For controls, a single household visit and interview will be done. The interviews will be structured (see Project 1 Interview,
*Extended data*)
^29^ and gather data on: i) socioeconomic position, evaluated by a multi-dimensional poverty score
^6,
9,
13,
15^ assessing dwelling characteristics, assets, and access to amenities; ii) household structure, including distribution of age, sex, and employment of household members; iii) food expenditure and security; iv) costs of engaging with TB care including direct costs (e.g. medicines, clinic visits, food, and travel) and indirect costs (e.g. lost income), which will be evaluated using an adapted version of WHO’s TB Patient Costs Survey integrated into the interview
^22,
23^; v) coping strategies including dissaving (e.g. selling assets), schooldays lost, and temporary income-generating activities; vi) TB-related knowledge including understanding of transmission, prevention, and treatment of TB; vii) psychosocial situation evaluated through questions relating to social capital, quality of life, and stigma (Controls without TB will not be asked any questions about the impact that having TB disease has on their psychosocial situation); and viii) access and uptake of existing social protection schemes (whether TB-specific or TB-inclusive) and support for TB-affected households, evaluated through use of both closed ranking and open free-text questions to establish what socioeconomic and other support people with TB and their households receive or would like to receive.

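### Time-varying measures taken during treatment are compared with controls as social determinants of TB, but these contrasts cannot separate cause from consequence

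*Protocol article*

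**What the plan says.** The Study design section describes the case-control component as "a nested case-control study examining the social determinants of TB". The Secondary aims section lists the determinants to be compared. Alongside socioeconomic position, housing and TB knowledge, the list includes "comorbidities, quality of life, food security, and social capital) in people with TB versus people without TB". The Outcomes section repeats the determinants label for poverty level, education and food security. The Data analysis and statistical plan section names "Social determinants of TB including sociodemographic characteristics, socioeconomic position, stigma and social capital levels, and TB-related knowledge" and assigns chi-squared tests, ANOVA and multiple logistic regression to the comparison.

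On timing, the Study population section says: "During months three and six of their TB treatment, household visits will be conducted by BNMT project staff". The Study activities section says of the other group: "For controls, a single household visit and interview will be done". No visit to cases before treatment is described. The article does not say which of the two case visits enters the comparison with controls.

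**The concern.** A determinant has to precede the disease. By month three of treatment a case household has been through the illness, any loss of income, any sale of assets and a period of contact with TB services. The current state of such a household is then set against a single control interview.

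The article supplies the reason for doubt. Its Introduction states: "Having TB disease can also worsen impoverishment through loss of income and costs of accessing care". It also cites a Nepalese cohort in which the total costs of care came to nearly a quarter of annual household income. Food security, quality of life and stigma can plausibly change after diagnosis too. TB knowledge may shift the other way through contact with care, although the article does not say so.

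At stake is what the secondary aim can conclude. An association could appear where none existed before illness. The findings also feed forward: Project 1's early results inform the Project 2 coding, and the study's evidence is meant to shape a future trial. Whether a factor precedes TB or follows from it bears on whether support should aim at prevention or at mitigation.

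**Working it through.** The article gives no power, alpha or effect size for this comparison, so there is no figure to reproduce. The check has two parts.

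**1. Is the same construct treated as both cause and effect?**

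- *Socioeconomic position.* Study activities scores it on dwelling, assets and amenities. The same list records the sale of assets as a coping strategy. The Discussion sets out to study the effect of TB on this position, while the analysis section lists it as a determinant. A household that sold assets because of TB would look poorer in the determinants comparison.
- *Pre-illness reference.* The only one stated is reported pre-TB income. It is used to estimate lost income, not in the case-control comparison.
- *Caveats.* The stated limitation on controls concerns convenience sampling and representativeness. Nothing addresses reverse causation, and neither a better control sample nor covariate adjustment would remove it.
- *Variables little affected.* These are education, other stable sociodemographic items and most dwelling features.

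**2. How large could a spurious association be?** This is an illustration.

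Inputs from the article: about 200 cases (ACF and PCF pooled here) and 100 controls. Assumed inputs: a share p0 of controls is poor; cases had the same share before illness; illness moves a share s of non-poor case households into poverty; two-sided alpha is 0.05.

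Formulas:
- p1 = p0 + (1 − p0) × s
- OR = [p1/(1 − p1)] / [p0/(1 − p0)]
- SE = √[p0(1 − p0)/100 + p1(1 − p1)/200]
- chance of p<0.05 ≈ Φ[(p1 − p0)/SE − 1.96]

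With p0 = 0.30, the control odds are 0.30/0.70 = 0.4286:

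| s | p1 | OR | SE | (p1 − p0)/SE | Chance of p<0.05 |
|---|---|---|---|---|---|
| 10% | 0.37 | 0.5873/0.4286 = 1.37 | 0.0571 | 1.22 | 23% |
| 20% | 0.44 | 0.7857/0.4286 = 1.83 | 0.0577 | 2.43 | 68% |
| 30% | 0.51 | 1.0408/0.4286 = 2.43 | 0.0579 | 3.63 | 95% |

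Using the pooled variance under the null gives 22%, 65% and 94%.

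Varying p0 from 20% to 50% (pooled variance):

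| s | OR, p0 = 20% to 50% | Chance of p<0.05 |
|---|---|---|
| 10% | 1.56 to 1.22 | 32% to 13% |
| 20% | 2.25 to 1.50 | 83% to 38% |
| 30% | 3.14 to 1.86 | 99% to 70% |

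For a continuous score that illness shifts by 0.2, 0.3 or 0.5 SD, the chance is 37%, 69% or 98%.

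**The case against.** The strongest reply is that this is a matter of labelling. The study calls itself exploratory, and the aim is worded as a comparison. The Discussion describes the case-control element without the word determinants, and the Project 2 analysis section mentions both determinants and consequences. A reader might infer that consequences will be reported as causes. No passage says so, and the documents support only that they may be read that way. What survives is that the causal label is attached to the design, the aim, the outcomes and the analysis, with no caveat at any of them.

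A reader might also infer that stigma and quality of life are scored on different item sets in the two groups, because "Controls without TB will not be asked any questions about the impact that having TB disease has on their psychosocial situation". That sentence says only that controls skip questions on the impact of TB. Controls may well receive the remaining items, and the questionnaire is not shown. Nor does the article say that counselling is measured, so any effect of care on knowledge is a plausible inference and no more.

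The size is also open to challenge. The poverty score is not an income measure, and of its components only assets are shown in the article to be depleted by illness. Costs near a quarter of annual income do not imply that 10% to 30% of non-poor households become poor on that score. This stands: the figures show that the bias is possible, not how large it is here.

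**Conclusion.** The point holds in a limited form. For current assets, food security, quality of life, stigma, social capital and TB knowledge, a difference between cases in treatment and controls cannot identify a determinant of TB. The article's own statements about the effect of TB on households give the reason. The point does not extend to education or to most dwelling features.

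The odds ratios of 1.37 to 2.43 rest wholly on assumed values for baseline poverty and for the shift caused by illness. They are not estimates for this study. The conclusion on time order does not depend on them. It would weaken for any item that the unseen questionnaire asks about the period before TB, but the article states such a reference for income only. The change should be made because it alters what the secondary aim can claim.

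**What to change.** In Secondary aims, Outcomes to be measured, and Data analysis and statistical plan:

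1. Restrict the determinants analysis and its logistic models to variables fixed before illness: education, other stable sociodemographic items and dwelling features.
2. Use reported pre-TB income as a sensitivity analysis only, because recall would differ between cases and controls.
3. Correct asset scores for assets sold since illness only if the dissaving items were recorded in enough detail. The article shows that dissaving is recorded, but not that the earlier asset holding can be rebuilt.
4. Report food security, quality of life, stigma, social capital, TB knowledge and current assets as case-control differences during treatment. Use the month-3 visit and only items asked of both groups, and state that cause and consequence cannot be separated.

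The cost is rewording and some derivation of variables. No new data are needed. This matters because the Study status section reports that Project 1 collection is nearly complete, while analysis was still to begin. The downside is fewer variables under the determinants heading, and recall error in pre-TB income.
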